### Eligibility criteria

We defined the eligibility criteria (Table 1) in order to minimize inclusion bias and to obtain 'representative’ data. The definitions stipulated in the SCIentinel protocol are consistent with previously published studies [6,8,18,30]. It was necessary to exclude patients with severe, life threatening polytrauma or severe TBI in order to limit variability caused by concomitant injury. For detection of immune system functionality, it is furthermore essential to exclude all circumstances combined with pre-existing alterations in the immunological profile such as chronic autoimmune diseases and pre-existing systemic treatment with corticosteroids.

The administrative interim analysis of the SCIentinel trial has confirmed the feasibility of the eligibility criteria. From August 2011 to April 2013 n = 64 patients have been enrolled for the study which represent 37 patients per year. Thus, the enrolment status is within the expected range. Four of the 64 patients (6%) were treated with high-dose methylprednisolone. Therefore, those patients are to be excluded from the 'per protocol’ analysis. However, casuistic studies on immunosuppressive effects of methylprednisolone treatment in the context of the SCI-IDS are enabled. The remaining 60 patients represent 51% of the estimated sample size (Table 4).

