**Discussion:**

The objectives are to characterize the dysfunction of the innate and adaptive immune system after spinal cord injury and to explore its proposed 'neurogenic’ origin by analyzing its correlation with lesion height and severity. The trial protocol considers difficulties of enrolment in an acute setting, and loss to follow up. The administrative interim analysis confirmed the feasibility of the protocol. Better understanding of the SCI-IDS is crucial to reduce co-morbidities and thereby to attenuate the impact of disease modifying factors to protect neurological “outcome at risk”. This putatively results in improved spinal cord injury medical care.

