### Duration

A recruitment period of 30 months is scheduled. Each patient will be followed-up to three months post-trauma. After completion of recruitment and follow-up, a further six months period is planned for the database clearing, the statistical evaluation and the preparation of the trial report. Enrolment has started in August 2011. Expected study completion date is the first quartile of 2014. Publication of the trial report is scheduled for the end of the year 2014.

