### Participants

A number of 118 patients is planned to be allocated to the study for examination of the primary endpoint. In order to allow for investigation of the role of disturbed innervation of the major splanchnic nerve (T5-T9) as linked to alterations of the immune system function, we categorize SCI patients into lesions with the neurological level T4 or above versus lesions neurological level T5 or below. Therefore, the patients will be assigned to 3 groups: i) 48 SCI-patients with a neurological level T4 or above; ii) 31 patients with a neurological level T5 or below; iii) 39 patients with an acute vertebral fracture, but without SCI as control group (Figure 2).

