### Enrolment and eligibility criteria

With the seven study centers treating 20 to 60 acute SCI patients admitted to the emergency ward of each center per year we estimate to screen about 200 SCI patients per year and about 40 of them are expected to meet eligibility criteria (Table 1).

**Table 1 T1:** Eligibility criteria

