### Interim evaluation of recruitment status

An administrative interim evaluation for control of the estimated recruitment schedule after enrolment and follow up of approximately 50% of the calculated sample size has been performed. Patients recruited until April 2013 and followed up to July 2013 were included. The groups for comparison were analyzed for their concordance with the estimated sample size (Table 4). Furthermore the completeness of data for the main laboratory outcome parameters (flow cytometry) at each time point was assessed within the 'per protocol’ population (Table 5).

**Table 4 T4:** Administrative interim analysis of the recruitment status for patients without high-dose methylprednisolone treatment

**Groups**	**Overall n (%)**	**SCI T4 and above n (%)**	**SCI T5 and below n (%)**	**Control group n (%)**	**Drop out n**
**Estimated sample size**	118 (100)	48 (100)	31 (100)	39 (100)	n.a.
**Enrolled partients**	60 (51)	28 (58)	11 (35)	17 (44)	4

**Legend:** Sixty patients without high-dose methylprednisolone treatment were included into the SCIentinel trial from August 2011 to April 2013. The number of patients recruited into the group of SCI patients of the neurological level T5 or below was slightly smaller than expected. This does not match the natural distribution of the lesion level and seems to be random. In total, four patients (7%) dropped out of the interim analysis due to occurrence of exclusion criteria.

**Table 5 T5:** Administrative interim analysis of the completeness of laboratory data (flow cytometry) for each visit relative to the number of enrolled patients feasible for 'per protocol’ analysis

**Groups**		**Visit 1**	**Visit 2**	**Visit 3**	**Visit 4**	**Visit 5**
**Overall** n = 56	Complete data n	32	38	44	44	25
	(% of 'per protocol’ population)	(57)	(68)	(79)	(79)	(45)
**SCI T4 and above** n = 28	Complete data n	17	20	22	22	16
	(% of 'per protocol’ population)	(61)	(71)	(79)	(79)	(57)
**SCI T5 and below** n = 11	Complete data n	6	6	8	10	5
	(% of 'per protocol’ population)	(55)	(55)	(73)	(91)	(45)
**Control group** n = 17	Complete data n	9	12	14	12	4
	(% of 'per protocol’ population)	(53)	(71)	(82)	(71)	(24)

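### The interim finding that enrolment is on course does not follow from the article's own figures: 118 patients in 30 months needs about 47 per year, and 37 were enrolled

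*Protocol article*

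**What the plan says.** **Plan.** Duration: "A recruitment period of 30 months is scheduled" and "Enrolment has started in August 2011", with completion expected in the first quarter of 2014. Participants: "A number of 118 patients is planned to be allocated to the study for examination of the primary endpoint". The groups are 48 with neurological level T4 or above, 31 with T5 or below, and 39 vertebral-fracture controls. Up to 12 methylprednisolone patients come on top of the 118.

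**Forecast.** Enrolment and eligibility criteria: "we estimate to screen about 200 SCI patients per year and about 40 of them are expected to meet eligibility criteria". This is the only annual enrolment forecast in the article.

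**Interim result.** The Discussion subsection Eligibility criteria reports 64 patients enrolled from August 2011 to April 2013, which it gives as 37 per year. Four of them received methylprednisolone, and the other 60 are 51% of the target. It concludes: "Thus, the enrolment status is within the expected range". Table 4 splits the 60 into 28 (T4 or above), 11 (T5 or below), 17 controls and 4 drop-outs. The Discussion paragraph of the Abstract adds: "The administrative interim analysis confirmed the feasibility of the protocol".

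**The concern.** The article gives a target, a recruitment period and an observed rate, and the three do not fit together. April 2013 is about month 21 of 30, yet only about half of the target had been enrolled. No extension, reduced target or expected acceleration is stated. The remedies under Observation period (earlier enrolment after injury, travel to rehabilitation centres, reminder calls) address missing visits, not the number recruited.

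Two things are at stake. One is a stated size and completion date that the observed rate does not deliver. The other is the T5-or-below group, on which the comparison of rostral with caudal lesions depends and which is furthest from its target.

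**Working it through.** **Inputs.** Target 118 (48/31/39) from Participants; 30 months from August 2011 from Duration; 64 enrolled, 4 of them on methylprednisolone, from the Discussion; 28/11/17 and 4 drop-outs from Table 4; complete flow cytometry by visit from Table 5; 56 evaluable required and 50% loss assumed from Sample size calculation.

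**1. The article's figures reproduce.** August 2011 to April 2013 inclusive is 21 months. 64/21 × 12 = 36.6, printed as 37 per year. 60/118 = 50.8%, printed as 51%.

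**2. Required against observed rate.** Required: 118/2.5 = 47.2 per year. Observed among those who count towards the 118: 60/21 × 12 = 34.3 per year. Time used: 21/30 = 70%. On-schedule count at month 21: 118 × 0.70 = 82.6, against 60.

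**3. By group** (observed n/21 × 12; required target/2.5; projection n/21 × 30):

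| Group | Enrolled / target | Observed per year | Required per year | Month 30 |
|---|---|---|---|---|
| T4 or above | 28 / 48 | 16.0 | 19.2 | 40.0 |
| T5 or below | 11 / 31 | 6.3 | 12.4 | 15.7 |
| Control | 17 / 39 | 9.7 | 15.6 | 24.3 |
| Drop-outs | 4 / – | – | – | 5.7 |
| All | 60 / 118 | 34.3 | 47.2 | 85.7 |

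The three groups sum to 80. The remaining 6 of the 86 are projected drop-outs.

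**4. Sensitivity of the projection to month 30.**

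| Elapsed months | n = 64 (all) | n = 60 (no methylprednisolone) | n = 56 (also no drop-outs) |
|---|---|---|---|
| 21 | 91 | 86 | 80 |
| 20 | 96 | 90 | 84 |

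No variant reaches 118. Time to 118 is 118/(60/21) = 41.3 months, with a range of 36.9 (64 in 20 months) to 44.2 (56 in 21 months).

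**5. What the last nine months would need.** (118 − 60)/9 = 6.4 per month, against 60/21 = 2.9 observed. The upper exact Poisson 95% limit for a count of 60 is 77.2, or 3.7 per month. That gives 33 in nine months, where 58 are needed, so chance variation around the observed rate does not close the gap.

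**6. Against the forecast of 40 per year.** The forecast is worded for SCI patients. Identified SCI enrolment is 28 + 11 = 39, and 39/21 × 12 = 22.3 per year. If all 4 methylprednisolone patients and all 4 drop-outs were SCI, it is 47/21 × 12 = 26.9 per year. If the 40 covered all groups instead, 40 × 2.5 = 100, still short of 118.

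**7. Evaluable patients at month 30.** The primary sample is placed at day 3–4, between visit 2 (31–55 hours) and visit 3 (day 7), so both are shown.

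| | Visit 2 | Visit 3 | Planned |
|---|---|---|---|
| All groups | 38/21 × 30 = 54 | 44/21 × 30 = 63 | 56 |
| T5 or below | 6/21 × 30 = 8.6 | 8/21 × 30 = 11.4 | 56 × 31/118 = 14.7 |

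With the effect size of 0.18 read as f² (an assumption, under which 56 gives the planned power), the power of the one-way ANOVA is 0.778 at 54, 0.795 at 56 and 0.845 at 63.

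**The case against.** **No benchmark is named.** The sentence does not say what range was expected. That it means the 40 per year is an inference, and if the 40 covered all groups, 37 would be close to it. This stands, so the comparison of SCI patients with SCI patients is secondary. It does not rescue the conclusion, because the shortfall against 47 per year needs no reading of the 40.

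**Power is not lost.** A reader might infer that closing at 30 months leaves too few evaluable patients for the primary test. The documents do not support that. Losses were planned at 50%, while 7% dropped out and visit 2 to 4 completeness was 68% to 79%. A deficit appears only with visit 2 and 21 elapsed months (54). With 20 elapsed months visit 2 gives 38/20 × 30 = 57, and visit 3 gives 63 even at 21 months.

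**The T5-or-below wording.** A reader might also infer that the Table 4 legend is false in saying: "The number of patients recruited into the group of SCI patients of the neurological level T5 or below was slightly smaller than expected". Against the schedule 11 is about half of 31 × 0.70 = 21.7. But the legend discusses the distribution across lesion levels. By planned share, 14.7 of the 56 assigned patients would be expected, and the binomial probability of 11 or fewer is about 0.16. The table prints 11 and 35% openly. The wording is defensible on that reading and is not part of this point.

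**Scope.** This is an observational study, the interim was a recruitment check, and the counts and dates are disclosed. No analysis becomes invalid. That limits the weight of the point but does not make the sentence correct.

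**Conclusion.** The statement that enrolment is as expected, and the Abstract's claim of confirmed feasibility, are wrong as written if they refer to 118 patients in 30 months. At the observed rate about 86 (80 to 96) would be enrolled by month 30, and completion in the first quarter of 2014 with 118 patients is not achievable. If the 40 per year is the benchmark, as its wording suggests, SCI enrolment was 22 to 27 per year against it.

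The practical loss is in the T5-or-below group: about 16 assigned and roughly 9 to 11 evaluable, against about 15 planned. The three-group test is close to its planned power.

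This rests on a constant enrolment rate and on visits 2 and 3 as stand-ins for the day 3–4 sample. Later acceleration is possible, but the article does not argue for it. How the drop-outs and methylprednisolone patients split between SCI and control is not given, which is why the SCI rate is a range.

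**What to change.** - Replace the sentence with the enrolment rate by group set against the required rate (16.0, 6.3 and 9.7 per year against 19.2, 12.4 and 15.6), and state that any projection assumes a constant rate.
- Restate one of two things: the recruitment end date, or the total and group sizes expected at 30 months with the resulting precision for comparisons that involve the T5-or-below group. Bring the Abstract and Duration into line.
- If the end date is moved to reach 118, say what that does by group. At about 41 months the same rates give 11/21 × 41.3 = 22 of 31 in T5 or below and 17/21 × 41.3 = 33 of 39 controls, so a longer period alone does not restore the planned group sizes.
- Monitor recruitment per group by patients with an evaluable primary sample, not by total enrolled.

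Cost: restated figures and a less favourable feasibility statement. Keeping the 118 also costs about 11 further months of recruitment at the observed rate. Keeping the 30 months costs no extra time, but means accepting the smaller groups.

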### Observation period

Observational time points (Figure 2) range from acute to sub-acute stages after SCI comparable to the pilot study [6]. Here, the time schedule corresponded to the hallmarks of parenchymal inflammation following SCI. The implementation of sub-acute assessments is in line with previous trials that demonstrated mid- and long-term alterations of the immune system after SCI [8,18,19].

The setting of defined time corridors instead of time points provides a more complete tracking of the participants. In order to prevent a high amount of missing datasets due to loss to follow-up, the protocol allows an inclusion at each documentation time point.

The administrative interim analysis of data completeness for the main laboratory parameters indicates - depending on the group or visit – a completeness of data between 24% and 91% with critical rates of completeness at visit 1 and visit 5, particularly in the control group (Table 5). As a consequence, the recruiting centers have been requested to enroll the patients as soon as possible after injury. Additionally, we intend to address the challenge of loss to follow up by travelling to external rehabilitation centers or by phone calls to remind patients of their study visit at the outpatient clinic. The rate of complete longitudinal datasets ranges between 18% and 36% but is expected to increase during the further trial course since trial routines are better established. Noteworthy, the sample size calculation takes 50% of missing values into account and was performed for one-way ANOVA. Repeated measure analysis requires lower sample sizes. Therefore, it seems feasible that a relevant amount of complete longitudinal datasets can be achieved also for the description of the intra-individual course of the SCI-IDS. Pursuing this study concept, serial investigations on short- and mid-term changes of the immunological function are provided.

### Clinical observations

For the clinical research, it is imperative to use reliable reproducible clinical tests. The ISNCSCI standards revised over the years to provide better, more specific definitions [23,24]. We incorporated the AIS and the single neurological level into the trial protocol for neurological baseline characterization of SCI patients.

The determination of infections is of crucial importance in this study. Prevailing infectious complications of SCI patients are pulmonary and urinary tract infections [4]. Cameron and colleagues recently provided a review consisting of 12 articles of urinary tract infection (UTI) screening for SCI [31]. Noteworthy, there is no universal definition of UTI used in the literature allowing substantial heterogeneity. The American Paraplegia Society (APS) recommends to base the diagnosis of UTI solely on bacteriuria, with a threshold of 10^2^ colony-forming units (cfu)/mL for SCI patients [32]. However, up to 75% of samples taken from asymptomatic SCI male patients under intermittent catheterization contain ≥ 10^2^ cfu/mL [32]. Thus, a threshold of 10^2^ cfu/mL is associated with low specificity, leading to an excess of treatment, with the risk of the emergence of resistant bacteria, adverse events, and unnecessary expense. In consequence, we defined according to the National group on urologic rehabilitation of paraplegics urinary tract infection as bacteriuria greater than 10^5^ cells/ml or WBC count of more than 100/mm^3^[21].

Regarding the development of chest infection criteria defined by Mann et al. were incorporated [22]. For the diagnosis of pneumonia the finding of infiltrates or opacity in chest X-ray will be required consistent with Haeusler et al. who used similar criteria in the analysis of cellular immunodepression preceding infectious complications after acute ischemic stroke [15].

In summary, the clinical assessments and definitions used in the SCIentinel study allow for collection of reliable and reproducible data.

### Primary outcome measure

For meeting the purpose of a more comprehensive characterization of the SCI-IDS and establishing prognostic surrogate parameters, it is essential to implement specific parameters, readily validated in clinical immunology, robust and reproducible [14]. Quantification of immune cell populations in the blood using FACS is a clinically established and precise method that qualifies as primary outcome measure. Our primary measure is the determination of HLA-DR-molecules per monocyte. Alterations in HLA-DR expression on monocytes occur early enough to identify patients at high risk for relevant immune depression and consecutive development of infections. Significantly decreased monocytic HLA-DR levels have been observed as early as day one after acute cerebral ischemia in patients who developed infectious complications in comparison to patients with an uncomplicated clinical course [27]. Furthermore, the method is already established and available in centralized immunological laboratories. It has sufficient diagnostic specificity as a basis for clinical decision-making and therefore is clinically highly relevant. Moreover, we implemented a large setting of secondary endpoints for the development of very early predictive parameters, for example on the level of mRNA expression.

### Possible consequences

The objective of this study is the longitudinal characterization of immunological markers of the innate and acquired immune system after traumatic SCI. Furthermore, the aim is to detect diagnostic surrogate parameters for the clinical application after SCI. The characterization of a causative relationship between the lesion level and/or SCI severity and the type and/or extent of the immune response after SCI - including a critical characterization of the methylprednisolone effect - is essential for the implementation of therapeutic studies. Understanding and recognition of the immunological dysfunction and the altered susceptibility to infections may then assist in consecutive decision-making. This is relevant for the stratification of patients who are at high or low risk for infectious complications [33]. In addition, these findings may also hold the key for early therapeutic immunomodulation aiming to improve overall survival by anticipation and prevention of life-threatening infectious complications.

## Abbreviations

ASIA: American Spinal Injury Association; AIS: ASIA impairment scale; BCT: Blood collection tube; CON A: Concanavalin A; CRF: Case report form; CRP: C-reactive protein; FACS: Fluorescence-activated cell sorting; EDTA: Ethylenediaminetetraacetic acid; GCP: Good clinical practice; HLA: Human leukocyte antigen; ISNCSCI: International standards for neurological classification of spinal cord injury; LPS: Lipopolysaccharides; PBMC: Peripheral blood mononuclear cell; PE: Phycoerythrin; SCI: Spinal cord injury; SCI-IDS: Spinal cord injury – induced immune depression syndrome; SEB: Staphylococcal enterotoxin B; TBI: Traumatic brain injury; UTI: Urinary tract infection.
